Taken together, the present trial will examine the efficacy of cognitive training on episodic memory of aMCI patients. If cognitive training is effective in improving episodic memory function, then greater improvement should be observed in the training group than control group. Moreover, functional and structural data would provide further neural plasticity information about the training-related improvement.

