### Intervention

Cognitive control training will be conducted using a computerized self-adaption training pattern (i.e. individually adjusted task difficulty to bring individuals to their performance maximum). Training tasks which were effectively used in previous studies will be adopted [36], including Flanker task [37], n-back working memory task [38], task switching [39], and Stroop task [40]. To guarantee adaptability to training difficulty, different levels of difficulty will be established as in previous studies with larger sample sizes. Briefly, at the beginning, each individual is assigned a task of similar difficulty. On each training day, the participants are required to complete five tasks three times, with 2 min for each training session (for a total daily test time of 30 min). For each task, the task difficulty will be advanced when the accuracy rate exceeds 80%. To adjust for individual variation in adaptability, the number of types of stimuli, the presentation probability of each type of stimuli, and the size and duration of a stimulus were systematically set. To keep a systematical setting, only one parameter will be adjusted; the remaining parameters will remain unchanged when the task difficulty is elevated. If the accuracy rate of a certain task exceeds 80% of normal counterparts, the task will be substituted for another of higher difficulty. The training program will be implemented five times weekly for 12 consecutive weeks.

In the control group, the training tasks include just the Flanker task and 1-back task. Importantly, a fixed, primary difficulty level will be set. The training tasks will be performed five times weekly, 30 min per session, for 12 consecutive weeks.

With the guidance of doctors, the initial training will be done in clinic and the rest of the training will be completed at home. The training will be supervised by an independent neurologist by telephone and the Internet.

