### Primary outcome measures

The primary outcome measure is memory retrieval function assessed by delayed recall of Auditory Verbal Learning Test-Huashan version (AVLT-H). To be specific, participants were asked to study a list of 12 frequent and concrete words three times. Words were presented acoustically and free recall was measured in an immediate recall condition, a 5-min short delayed recall condition, and a 20-min long delayed recall condition.

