### Sample size estimates

According to a previous study [41], in which computerized cognitive training was administered for six weeks, the mean difference in AVLT-H score between the cognitive training and control groups was 0.26 ± 0.3. Based upon this difference, 22 samples are required to yield a statistical power of 80% at a statistical significance level of 0.05. The sample size was estimated using the following equation:$$ n=\frac{\left({q_1}^{-1}+{q_2}^{-1}\right){\left({t}_{\alpha /2}+{t}_{\beta}\right)}^2{S}^2}{\delta^2} $$

where q_1_ and q_2_ are the sample size ratio of two groups (q_1_ = q_2_ = 0.5), α is the statistical significance level (α = 0.05), β is calculated from 1-β which stands for statistical power (1-β = 0.8), δ is the mean difference (δ = 0.26), and S is the standard deviation (S = 0.3) used in the analyses. Considering the instability of standard deviation and dropout rate, the sample size for each group is set as 35.

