### Statistical analysis

To make sure that baseline levels between groups (cognitive training, control) are comparable, questionnaire measures will be analyzed using independent sample t-tests. To determine the training efficacy from baseline to outcome, paired sample t-tests will be used in each group, respectively, for the changes in scores of trained tasks. The neuropsychological changes will be correlated with the score changes of the trained tasks to test the training effect on neuropsychological performance. To determine the training transfer effect, ANOVAs will then be performed on each dependent variable, with time (baseline, outcome) as the within-subjects factor and group (cognitive training, control) as the between-subjects factor.

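### A correlation between two post-randomisation change scores is given the job of testing the training effect on neuropsychological performance, which it cannot do, alongside a valid between-arm analysis.

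*Protocol article*

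**What the plan says.** The Statistical analysis section of the protocol article sets out three post-baseline analyses.

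- Trained tasks: "paired sample t-tests will be used in each group, respectively, for the changes in scores of trained tasks".
- Neuropsychological tests: "The neuropsychological changes will be correlated with the score changes of the trained tasks to test the training effect on neuropsychological performance". The article does not say whether this is done within each arm or across both.
- Transfer of training: an ANOVA on each dependent variable, "with time (baseline, outcome) as the within-subjects factor and group (cognitive training, control) as the between-subjects factor".

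Three other places bear on this. The Background gives the criterion for an effective intervention: "greater improvement should be observed in the training group than control group". Primary outcome measures names AVLT-H delayed recall, and Neuropsychological assessment lists the AVLT-H in the battery, so the correlation sentence covers the primary outcome. Intervention describes an adaptive programme of several tasks for the training group, while "In the control group, the training tasks include just the Flanker task and 1-back task", at a fixed difficulty.

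**The concern.** The trial's question is whether assignment to training changes memory performance. Randomisation protects the comparison of arms. It does not protect a comparison of patients by how much they gained on the tasks, because that gain is itself observed after randomisation. A patient who learns readily, is motivated, adheres well or benefits from repeated testing may improve on both the trained tasks and the neuropsychological tests, whichever arm he or she is in. A significant correlation is then real as a correlation, but it says nothing about what training did.

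An analysis described as a test of the training effect could therefore support an efficacy claim, including one on the primary outcome, when the arms do not differ. It could also fail to reach significance when they do.

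**Working it through.** **The trial's own design calculation.** Sample size estimates uses δ = 0.26, S = 0.3, two-sided α = 0.05, power 0.8 and q1 = q2 = 0.5. With normal quantiles the formula gives a total of (2 + 2) × (1.960 + 0.842)² × 0.3² / 0.26² = 41.8, or 21 per arm. With iterated t quantiles the total is 43.8, or 22 per arm. The stated 22 reproduces as a number per group. The sample size is not at issue. It confirms that the trial was sized for a difference in means between arms, which is not what the correlation estimates.

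**How often the correlation is significant with no effect of allocation.** The article gives no correlation r between the two changes, so r is assumed over a range. By Fisher's z, the statistic is approximately normal with mean atanh(r) × √(n − 3) and unit variance, and the probability of p < 0.05 is P(|Z| > 1.96). The planned n is 35 per arm, or 70 in all.

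- r = 0.2: 0.2027 × √32 = 1.147, giving 21%; 0.2027 × √67 = 1.659, giving 38%.
- r = 0.3: 0.3095 × √32 = 1.751, giving 42%; 0.3095 × √67 = 2.533, giving 72%.
- r = 0.4: 0.4236 × √32 = 2.397, giving 67%; 0.4236 × √67 = 3.468, giving 93%.

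A simulation checked this: 20,000 replicates per setting, bivariate normal changes with unit SD within each arm, 35 per arm, and no effect of allocation on either change. The between-arm test was a t-test on the neuropsychological change, which with two time points is equivalent to the time by group term.

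| Assumed r | Correlation, one arm (n = 35) | Correlation, pooled (n = 70) | Time by group |
|---|---|---|---|
| 0 | 5% | 5% | 5% |
| 0.2 | 21% | 38% | 5% |
| 0.3 | 43% | 72% | 5% |
| 0.4 | 68% | 94% | 5% |

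Simulation and formula agree to within about one percentage point. If training moves the trained tasks by 1 SD but the neuropsychological score not at all, the pooled rates for r = 0.2, 0.3 and 0.4 are 31%, 62% and 87%. The time by group test stays at about 5%.

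**How often it misses a real effect.** Take a uniform benefit of the size used in the design, 0.26 / 0.3 = 0.87 SD, with no correlation between the changes within an arm.

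- Within the training arm everyone shifts by the same amount, so no correlation arises and the test is significant in 5% of trials.
- Pooled, with no shift in the trained tasks, it is also significant in 5%.
- Pooled, with a 1 SD shift in the trained tasks, the arm difference itself creates a correlation: r = 0.25 × 1 × 0.867 / √[(1 + 0.25 × 1²)(1 + 0.25 × 0.867²)] = 0.2167 / √(1.25 × 1.188) = 0.18. This is significant in about 32% of trials.
- The between-arm test is significant in about 95%.

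**Scale of the trained-task score.** If the arms were pooled, a further problem arises. The trained-task change comes from several adaptive tasks in one arm and two fixed-difficulty tasks in the other, so it is not the same variable in both.

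**The case against.** The strongest reply is that the randomised test is already planned. The ANOVA applies to each dependent variable. The Background uses transfer for abilities not directly trained, with delayed recall among its examples, and AVLT-H delayed recall is not one of the trained tasks. In the article's own terms, then, the transfer ANOVA covers the primary outcome. This stands. A reader might infer from the correlation sentence that no between-arm test of neuropsychological benefit exists, and the article does not support that. Nor does it make the correlation the primary or deciding analysis.

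Second, the article does not say the arms are pooled, and the preceding sentence works within each group. This also stands. The pooled figures and the point about differing task scores are conditional on pooling.

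Third, a reader might conclude that a benefit common to all trained patients can never show as a correlation. That is true within an arm. It is not true of a pooled analysis in which the trained tasks also shift, as the 32% shows.

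Fourth, the percentages are simply the power to detect a correlation that has been assumed. That is right: they are not estimates for this trial, and at r = 0 there is no excess. They become false claims of efficacy only because the plan gives the correlation that meaning.

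None of this rescues the clause itself. It states a purpose that the method cannot serve. An analysis plan not shown here could add detail, but it would have to contradict the sentence to correct it.

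**Conclusion.** The point holds as a mislabelled, competing inference, not as a missing between-arm analysis. The Statistical analysis section attaches an efficacy claim to two analyses: the ANOVA addresses the Background's criterion of greater improvement in the training group, and the correlation does not.

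The direction of the fault does not depend on any assumed figure: whenever the two changes share causes, the correlation is significant more often than 5% of the time with no effect of allocation. Its size does depend on r, which the article does not give. Over r from 0 to 0.4 the rate runs from 5% to 67% within an arm of 35, and from 5% to 93% if all 70 patients were pooled. These figures assume bivariate normal changes and full follow-up. The opposite error, 5% to 32% detection against about 95% for the between-arm test, assumes a uniform benefit of 0.87 SD and no within-arm correlation.

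Because a valid test is already in the plan, the consequence is limited to how the correlation may be interpreted. It should still be corrected, since the sentence covers the primary outcome.

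**What to change.** In the Statistical analysis section:

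1. Delete the clause that makes the correlation a test of the training effect on neuropsychological performance.
2. State that the effect on neuropsychological measures, including AVLT-H delayed recall, is assessed only by the between-arm comparison. The time by group term already planned is sufficient; the outcome score adjusted for its baseline value would be preferable.
3. Describe the correlation as an exploratory association, computed within arm. Adjusting it for age or education is optional and is not needed to cure the fault.

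The cost is analysis wording only. No data, visits or sample size change.

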**Methods/Design:**

In this single-center, randomized double-blind placebo-controlled study, 70 aMCI patients will be recruited and randomly assigned to the training and control groups. The intervention is an Internet-based cognitive control training program performed for 30 min daily, five days per week, for 12 consecutive weeks. Neuropsychological assessment and structural and functional magnetic resonance imaging (MRI) will be performed at baseline and outcome. Primary outcomes are changes of episodic memory retrieval function. Secondary outcome measures are neuroplasticity changes measured by functional and structural MRI.

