### Inclusion criteria

Age > 55 years;Elementary school education or higher;Chief complaint of memory impairment confirmed by relatives;Ability to read a computer screen;Normal overall cognitive function as evidenced by Clinical Dementia Rating-global (CDR-global) = 0.5, Mini-mental State Examination (MMSE) score ≥ 22 with a concurrent Montreal Cognitive Assessment (MoCA) score ≤ 20 for those with elementary educational level and MMSE score ≥ 26 with a MoCA score ≤ 25 for those with junior educational level or above;Auditory Verbal Learning Test-Huashan version (AVLT-H) scores 1.5 standard deviations lower than age-matched controls;Activities of Daily Living assessment-20 (ADL-20) ≤ 23;Do not comply with AD diagnostic criteria proposed by the International Statistical Classification of Diseases and Related Health Problems, 10th Revision (ICD-10 for research use) and the National Institute of Neurological and Communicative Disorders and Stroke and Alzheimer’s Disease and Related Disorders Association (NINCDS-ADRDA).

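### The between-arm effect is tested by a time-by-group ANOVA, a valid change-score test, when adjusting for the baseline AVLT-H would be at least as precise; the baseline t-tests cannot establish that the arms are comparable

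*Protocol article*

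**What the plan says.** The Statistical analysis section of the protocol article fixes the between-arm method for every outcome: "ANOVAs will then be performed on each dependent variable, with time (baseline, outcome) as the within-subjects factor". The second factor in the model is given as "group (cognitive training, control) as the between-subjects factor". It names no baseline covariate, and no other section supplies one.

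The same section opens with a check on the arms: "To make sure that baseline levels between groups (cognitive training, control) are comparable, questionnaire measures will be analyzed using independent sample t-tests". It does not say what follows if a test is significant.

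Under Primary outcome measures: "The primary outcome measure is memory retrieval function assessed by delayed recall of Auditory Verbal Learning Test-Huashan version (AVLT-H"). The abstract frames this as change: "Primary outcomes are changes of episodic memory retrieval function". It also says that "Neuropsychological assessment and structural and functional magnetic resonance imaging (MRI) will be performed at baseline and outcome". Data collection and Neuropsychological assessment confirm that the AVLT-H belongs to the battery repeated after 12 weeks. The baseline value of the primary outcome is therefore already planned for collection.

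One entry criterion uses the same instrument: "Auditory Verbal Learning Test-Huashan version (AVLT-H) scores 1.5 standard deviations lower than age-matched controls". It does not say which AVLT-H score is meant.

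**The concern.** In a two-arm trial with one baseline and one follow-up measurement, the interaction term of the planned ANOVA is the comparison of mean changes. Subtracting the whole baseline value is the best use of it only if the regression of outcome on baseline has slope 1. A memory score measured twice with error will usually have a slope below 1. Subtraction then over-corrects: it adds baseline noise to the estimate and passes part of any chance baseline difference into it.

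The t-tests do not repair this. After randomisation, any baseline difference is due to chance, so the null hypothesis they test is already known to be true. Their p-values say nothing about how far the observed difference moves the treatment estimate. In a trial of 70, a non-significant result could be taken as reassurance while an imbalance large enough to matter remains.

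What is at stake is some precision on the primary comparison and how well the estimate withstands an unlucky allocation. The type I error rate is not at stake.

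**Working it through.** **Inputs.** From Sample size estimates: 35 per arm, difference 0.26, S = 0.3, power 80%, and "α is the statistical significance level (α = 0.05"), used two-sided. Rho is not in the document, so it is assumed over 0.5-0.8. Whether S is the SD of a change or of a single score is not stated.

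**1. The plan's own figure.** The stated formula is n = (1/q1 + 1/q2)(t_α/2 + t_β)²S²/δ² with q1 = q2 = 0.5.
- Normal quantiles: 4 × (1.960 + 0.842)² × 0.09/0.0676 = 41.8 in total, or 21 per arm.
- t quantiles (42 df): 4 × (2.018 + 0.850)² × 0.09/0.0676 = 43.8 in total, or 22 per arm.

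The stated 22 therefore reproduces as a per-arm figure. Exact power is 80.2% at 22 per arm and 94.7% at 35.

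**2. The planned test is the change-score test.** In 200 simulated trials of 35 per arm, the time-by-group F equalled the squared two-sample t on change scores, with a maximum difference of about 1e-14.

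**3. Precision, equal variances (no effect of the entry rule).** With score variance s²:
- Variance of change = 2(1 − rho)s²
- ANCOVA residual variance = (1 − rho²)s²
- Ratio = (1 + rho)/2

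At rho 0.5 the ratio is 0.75, so 35 per arm works like 35/0.75 = 47. At rho 0.7 it is 0.85, so 35 works like 35/0.85 = 41.

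**4. Precision, entry rule strictly truncating the same score.** Take a standard normal score cut at −1.5. The density-to-tail ratio is 1.939, so the remaining baseline variance is V = 1 + 1.5 × 1.939 − 1.939² = 0.150. With population slope rho:
- Variance of change = (1 − rho)²V + (1 − rho²)
- ANCOVA residual variance = 1 − rho²
- Ratio = (1 + rho)/[(1 − rho)V + 1 + rho]

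| rho | Ratio, equal variances | Ratio, strict truncation |
|---|---|---|
| 0.5 | 0.75 | 1.5/1.575 = 0.953 |
| 0.7 | 0.85 | 1.7/1.745 = 0.974 |
| 0.8 | 0.90 | 1.8/1.830 = 0.984 |

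Under truncation, 35 per arm works like about 37 (rho 0.5) or 36 (rho 0.7).

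**5. Shift from a chance imbalance.** The change-score estimate moves by (1 − slope) × imbalance. For an imbalance of 0.3 within-sample SD at rho 0.5:
- No truncation: 0.5 × 0.3 = 0.15 SD.
- Strict truncation: the within-sample baseline SD is √0.150 = 0.387, so the shift is 0.5 × 0.3 × 0.387 = 0.058 population SD. The outcome SD is √(0.25 × 0.150 + 0.75) = 0.887, so this is 0.065 outcome SD.

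**6. What the baseline t-test can see.** The standard error of a standardised baseline difference at 35 per arm is √(2/35) = 0.239.
- An observed 0.3 SD difference gives t = 0.3/0.239 = 1.255 on 68 df, p = 0.21. It is not flagged.
- The threshold for p < 0.05 is 1.995 × 0.239 = 0.48 SD.
- By chance, differences beyond 0.3 SD in either direction arise in about 21% of randomisations (normal approximation).

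**7. Power on the plan's inputs, reading S as the SD of change.** At 35 per arm the planned test has 94.7%. ANCOVA has 98.5% (rho 0.5) or 97.2% (rho 0.7) with equal variances. If dropout left 22 per arm, the figures are 80% against 90% or 86%.

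**The case against.** The strongest reply is that nothing here is invalid. The primary outcome is framed as change, the Background expects greater improvement in the training arm, and the interaction tests exactly that, without bias over randomisation and with the correct error rate. This stands. A reader might infer from the word shift that the planned estimate is biased. It is displaced only conditionally on the imbalance that happens to occur; averaged over allocations it is not.

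Second, the larger gain ignores the entry rule. This also stands in part. Because patients are selected on low AVLT-H, equal baseline and outcome variances cannot be taken for granted, and a gain of 2-5% is a live reading. The criterion does not say which AVLT-H score is used, whereas the outcome is delayed recall, so the true gain may lie between the two cases. A reader might argue the opposite: that selection lowers the correlation and so enlarges the gain through (1 + rho)/2. That formula needs equal variances, which selection removes. At population rho 0.5 the within-sample correlation falls to 0.5 × 0.387/0.887 = 0.22, which would give a ratio of 0.61, while the actual ratio is 0.953.

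Third, power already looks ample if S is the SD of change: 94.7% at 35 per arm. So the document does not support the inference that the trial is underpowered for want of ANCOVA.

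Three further inferences go beyond the text. The article does not say that the ANOVA main effects will be read as the treatment effect. It does not say that the t-tests decide whether to adjust. And the power of the t-test against a true 0.3 SD difference is the wrong measure of its weakness, because under randomisation no such population difference exists.

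Lastly, a fuller analysis plan might add covariates. But the article states a specific method; it does not leave the question open.

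**Conclusion.** The point holds as an improvement at almost no cost, not as an error that invalidates the analysis. The planned ANOVA is a sound test, but it fixes a slope that the data could estimate. Apart from one degree of freedom per covariate, ANCOVA is no less precise in any case examined.

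The size depends on two things the document does not settle: rho, and whether entry and outcome use the same AVLT-H score. The variance reduction runs from 2-5% (strict truncation, rho 0.5-0.8) to 15-25% (equal variances, rho 0.7-0.5). The protection against chance imbalance runs over a similarly wide range, from about 0.06 to 0.15 SD for a 0.3 SD imbalance at rho 0.5.

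The criticism of the baseline t-tests does not depend on either assumption. Testing a null known to be true cannot show that the arms are comparable, and at this size it passes any observed imbalance below about 0.48 SD.

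**What to change.** In the Statistical analysis section:

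- Make the primary analysis an ANCOVA of week-12 AVLT-H delayed recall on arm, with baseline AVLT-H delayed recall as a prespecified covariate. Age and education, both already collected, are optional additions.
- Report the adjusted between-arm difference with its 95% confidence interval.
- Use the same model for the other neuropsychological and MRI outcomes measured at both times.
- Replace the baseline significance tests with a descriptive table by arm.

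This needs no new data or visits. The cost is a change of wording and one degree of freedom per covariate.
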